#### EEG data

EEG data will be recorded using a 64-electrode Geodesic Sensor Net (Electrical Geodesics Inc., Eugene, OR, USA) connected to a high input-impedance Net Amps 400 amplifier (Electrical Geodesics Inc., Eugene, OR, USA). The EEG signals will be referenced to the vertex (Cz) and digitally sampled at 1 kHz using NetStation software (v.5.4, Electrical Geodesics Inc., Eugene, OR, USA). TTL pulses will be sent to the EEG recording system via an experimental synch Deutsches Institut für Normung (DIN) for synchronization of voice and EEG signals. The impedance levels of individual sensors will be kept below 50 kΩ throughout the recording, as this amplifier accepts scalp-electrode impedances up to 60 kΩ (Ferree et al., 2001).

The EEG signals will be analyzed offline using NetStation software. They will be band-pass filtered with cut-off frequencies of 1–20 Hz and segmented into epochs ranging from 200 ms before to 500 ms after perturbation onset. An artifact detection procedure will be applied to identify bad trials, during which trials whose voltage values exceed ± 55 μv of the moving average over an 80-ms window will be rejected from further analysis. After re-referencing to the average of the electrodes on each mastoid, artifact-free trials will be averaged and baseline-corrected (−200 ms to 0) to generate an overall ERP response for each condition. A total of 24 electrodes in three regions of interest (ROIs) will be selected for statistical analysis (Dai et al., 2022; Lin et al., 2022): frontal area, including AF3, AFz, AF4, F5, F3, F1, Fz, F2, F4, and F6; fronto-central area, including FC5, FC3, FC1, FCz, FC2, FC4, and FC6; and central area, including C5, C3, C1, Cz, C2, C4, and C6. The amplitudes and latencies of the P1, N1 and P2 components will be extracted from the averaged ERPs for each ROI.

#### MRI data

MRI data will be acquired using a 3.0 T Siemens magnetic resonance system (SIEMENS MAGNETOM Prisma, Germany). Participants will be instructed to stay awake with their eyes closed, refrain from thinking of anything, and remain motionless during the scanning session. Memory foam padding and earplugs will be provided to minimize head motion and scanner noise. To minimize fatigue and ensure that patients are in the “ON” state during MRI scanning, the scanning session will be scheduled on a different day from the other assessments. The following sequences will be acquired: (1) a high-resolution structural T1-weighted MPRAGE sequence will be used to acquire anatomical images with the following parameters: repetition time (TR) = 2,000 ms; echo time (TE) = 1.76 ms; flip angle = 8°; field of view (FOV) = 260 × 260 mm^2^; slice thickness = 0.6 mm; number of slices = 224; voxel size = 0.8 × 0.8 × 0.8 mm^3^. (2) resting-state fMRI data will be acquired using an EPI imaging sequence with the following parameters: TR = 2,000 ms; TE = 30 ms; flip angle = 90°; FOV = 224 × 224 mm^2^; voxel size = 3.5 × 3.5 × 3.5 mm^3^.

Statistical Parametric Mapping (v.12.0, Wellcome Trust Centre for Neuroimaging, London, UK) will be used for the preprocessing of rs-fMRI data on the MATLAB platform (MathWorks Inc., Natick, MA, USA). The preprocessing steps will include head motion correction, slice timing correction, spatial normalization, and smoothing. After preprocessing, the REST software (Song et al., 2011) will be used for connectivity analysis of brain functions. Regional homogeneity (ReHo) will be calculated using the Kendall coefficient of concordance (KCC) between the time series of a given voxel and those of its 26 neighboring voxels to reflect the local synchronization of spontaneous brain activity (Zang et al., 2004). ReHo maps between groups will be compared using voxel-wise two-sample *t*-tests in SPM with a significance level of *p* < 0.05. FC, which reflects the temporal correlation of spontaneous brain activity between different regions, will be calculated by Pearson’s correlation coefficient between the time series of a ROI and those of all other voxels in the brain. The right cerebellar hemisphere will be used as the ROI because it has been linked to speech and language functions (Marien et al., 2014; Moberget et al., 2014; Lesage et al., 2017; Argyropoulos et al., 2019; Diedrichsen et al., 2019). The ROI will be centered at MNI coordinate (42, -56, -30) and defined by a sphere with a radius of 6 mm. Correlation coefficients will be transformed to z-scores using Fisher’s r-to-z transformation to obtain z-FC maps for each participant. The contrast between z-FC maps post- and pre-intervention for each participant will be calculated to obtain Δz-FC maps, which will be used for a two-sample *t*-test to compare FC changes between the EG and CG groups. The statistical criterion will be set at *p* < 0.05, and false discovery rate (FDR) will be used for multiple comparisons correction.

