**Secondary outcomes**					
MDS-UPDRS-III	X			X	X
SCWT	X			X	X
QoL	X			X	X
fMRI scanning	X			X	X
**Safety**			X	X	X

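### ReHo is computed on already smoothed data, its scan time point and baseline handling are not fixed, and it is unclear whether the FDR correction covers it

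*Protocol article*

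**What the plan says.** All the relevant rules stand in one paragraph of the MRI data section of the Protocol article.

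- **Order of steps.** "The preprocessing steps will include head motion correction, slice timing correction, spatial normalization, and smoothing". Then: "After preprocessing, the REST software (Song et al., 2011) will be used for connectivity analysis of brain functions". ReHo is the first index described after that.
- **Definition.** ReHo is Kendall's coefficient of concordance (KCC) "between the time series of a given voxel and those of its 26 neighboring voxels to reflect the local synchronization".
- **ReHo test.** "ReHo maps between groups will be compared using voxel-wise two-sample" t-tests, continuing as "tests in SPM with a significance level of" p < 0.05. The sentence gives no time point, no pre/post contrast and no multiplicity correction.
- **FC test.** "The contrast between z-FC maps post- and pre-intervention for each participant will be calculated to obtain Δz-FC maps", and these change maps are compared between arms.
- **Closing criterion.** After the FC test the paragraph sets p < 0.05 with FDR correction, and does not say whether this covers ReHo, FC or both.

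The Resting-state fMRI section gives the purpose of the scans as detecting change after the intervention. It describes FC there in terms of local synchrony, which the MRI data section uses for ReHo.

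**The concern.** Three features of the ReHo analysis look wrong or unfixed.

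1. A smoothing kernel makes adjacent voxels agree. An index of agreement between adjacent voxels, taken after smoothing, therefore partly measures the kernel.
2. Each patient is to be scanned at three time points, but the ReHo comparison does not say which maps enter it. Baseline maps would carry no treatment effect and pooled maps would dilute one. The stated aim is change, and FC in the same paragraph has a change contrast.
3. The ReHo sentence carries its own complete voxel-wise threshold, and FDR is named only later. Taken at face value, tens of thousands of tests would be run at p < 0.05 each.

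At stake is the interpretation of the ReHo map as evidence on how cTBS works. The ReHo level would be hard to interpret, the choice of maps could be made after the data are seen, and chance voxels could be reported as findings.

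**Working it through.** The plan derives no figure for ReHo, so there is none to reproduce. The checks below size each feature.

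**1. Smoothing before KCC**

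From the protocol: 27 series per KCC (a voxel plus 26 neighbours) and 3.5 mm isotropic voxels. Assumed: Gaussian kernels of 4, 6 and 8 mm FWHM (the article gives no kernel size), white noise, 200 time points.

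KCC is linked to the mean pairwise rank correlation r among m series by KCC = [1 + (m − 1) r] / m. With independent series, r = 0 and KCC = 1/27 = 0.037. Simulated values, with r = (27 × KCC − 1) / 26:

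| Kernel (FWHM) | Mean KCC in pure noise | Implied r |
|---|---|---|
| none | 0.037 | 0.00 |
| 4 mm | 0.082 | 0.05 |
| 6 mm | 0.249 | 0.22 |
| 8 mm | 0.407 | 0.38 |

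A second simulation asked whether this harms a comparison. A shared local signal of strength 0.5 or 0.7 was added to the noise:

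| Kernel | KCC, weaker signal | KCC, stronger signal | Ratio | Difference in SD units |
|---|---|---|---|---|
| none | 0.223 | 0.339 | 1.52 | 5.6 |
| 6 mm | 0.835 | 0.905 | 1.08 | 5.7 |
| 8 mm | 0.927 | 0.961 | 1.04 | 5.4 |

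Smoothing first raises and compresses the index, but the standardised difference hardly moves.

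**2. Time point and baseline handling**

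From the protocol: randomised 1:1, 20 per arm. Assumed: a true effect of 0.8 SD and a range of pre-post correlations rho, which no document gives.

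- Bias: at rho = 0.7, over 5,000 simulated trials, the mean estimate was 0.79 both for the post-only and for the change comparison. Neither is biased.
- Variance of post-only relative to change = 1 / [2(1 − rho)]: 0.71 at rho = 0.3, 1.0 at 0.5, 1.67 at 0.7.
- Power for one test at two-sided 0.05, with SD 1 (post-only), sqrt[2(1 − rho)] (change) and sqrt(1 − rho²) (baseline as covariate):

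| rho | Post-only | Change | Baseline as covariate |
|---|---|---|---|
| 0.3 | 0.72 | 0.57 | 0.76 |
| 0.5 | 0.72 | 0.72 | 0.83 |
| 0.7 | 0.72 | 0.90 | 0.94 |

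These powers rank the methods. They are not the power of a corrected map.

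**3. Threshold**

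Assumed: 1.2 to 1.6 litres of brain in the mask. Voxel volume = 3.5³ = 42.875 mm³.

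- 1,200,000 / 42.875 ≈ 28,000 voxels; × 0.05 ≈ 1,400 expected false positives.
- 1,600,000 / 42.875 ≈ 37,300 voxels; × 0.05 ≈ 1,870, or about 1,900.
- If normalisation resamples to 3 mm (27 mm³), the counts are about 44,400 to 59,300 voxels and 2,200 to 3,000 false positives.

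In simulated null maps (32,000 independent voxels, 20 per arm), 1,570 to 1,636 voxels fell below 0.05. Benjamini-Hochberg FDR declared none.

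**The case against.** The strongest defence is that little of this damages the treatment comparison, and that some of it is only brevity.

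- **A reader might infer that the ReHo map could not show a treatment effect.** The documents do not support that. Allocation is randomised, so a post-intervention comparison is unbiased, and its p-value already allows for chance baseline differences. Smoothing is the same in both arms and left the standardised difference about unchanged. This part of the defence stands.
- **A reader might infer that raw post-intervention maps are compared and that change maps would always do better.** The text names no time point, so a post-only analysis is not shown. Change maps lose precision when the pre-post correlation is below 0.5. This also stands. What remains is that the time point and baseline handling are open for ReHo while they are fixed for FC.
- **A reader might take the ReHo test as definitely uncorrected.** The closing FDR sentence ends the paragraph that covers both indices, and it may reach ReHo. Against that, the ReHo sentence has its own threshold and the FDR sentence follows directly on the FC test. The uncorrected reading is the natural one, but not certain.
- **A reader might infer that the follow-up scans enter no analysis**, because Table 1 schedules "fMRI scanning" at W14 and the only contrast described is post minus pre. That rests on the silence of a condensed article, which need not list every contrast.
- **ReHo is minor.** It is named only in the MRI data section, and the Abstract lists functional connectivity as the imaging outcome. This limits the consequence.

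The order of steps, the neighbourhood, the test and the threshold are not matters of silence: the article states them.

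**Conclusion.** The point holds in a limited form.

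- **Smoothing.** As written, ReHo is computed on smoothed data, and its level then largely reflects the kernel: about 0.08, 0.25 and 0.41 in pure noise at 4, 6 and 8 mm, against 0.037 unsmoothed. Kernel sizes and the white-noise model are assumptions. This is a fault of measurement and interpretation, equal in both arms, not a between-arm bias.
- **Time point and baseline.** Neither is fixed for ReHo, although both are for FC and the stated aim is change. The loss is precision and pre-specification, not validity under randomisation.
- **Threshold.** Coverage of ReHo by the FDR rule is unclear. If it is not covered, about 1,400 to 1,900 false-positive voxels are expected under the null, given 1.2 to 1.6 litres and 3.5 mm voxels. If it is covered, this part falls away once the text says so.

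ReHo is a secondary, mechanistic analysis. The voice, vocal-response and ERP conclusions do not depend on it. The matter should be settled before unblinded analysis.

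**What to change.** 1. Compute ReHo on normalised, unsmoothed data and smooth the resulting ReHo maps. Smoothed data may still be used for the seed-based FC analysis.
2. State that post-intervention ReHo maps are compared between arms with each participant's baseline map as covariate. Change maps that match the FC analysis are an acceptable alternative, provided it is noted that they gain precision over a post-only comparison only if the pre-post correlation exceeds 0.5.
3. State that the FDR correction applies to the ReHo map as well as to the FC map.

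The cost is a change in pipeline order and a few sentences, with no new scans or participants. The downside is that fewer ReHo voxels will survive a corrected threshold.

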### Statistical analysis

Statistical analyses of clinical and behavioral parameters will be performed using SPSS software (v. 20.0). All patients with PD who have at least one post-intervention assessment will be included in the analysis. Gender differences between groups will be assessed using a chi-square test. Baseline measures will be compared between groups using two-sample *t*-tests. A 2 × 3 two-way repeated-measures analysis of variance (RM-ANOVA) with factors of group (real cTBS, sham cTBS) and time (pre-intervention, post-intervention, 12-week follow-up) will be used to investigate the effects of cerebellar cTBS on speech functions, neurobehavioral changes of vocal motor control, and quality of life. *Post hoc* pairwise correction will be performed using Bonferroni comparison adjustment. Pearson analysis will be used to examine correlations between neurophysiological and behavioral measures. A *p*-value < 0.05 in a two-tailed test will be considered statistically significant.

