## Materials and methods

### Study design

This study design adheres to a randomized, sham-controlled, single-center clinical trial, in accordance with the Standard Protocol Items Recommendations for Intervention Trails (SPIRIT) guideline (Chan et al., 2015). The study will be conducted in the Department of Rehabilitation Medicine at The First Affiliated Hospital of Sun Yat-sen University, China. The research protocol was approved by the Ethics Committee of FAH-SYSU (No. [2020]471). The trial was prospectively registered on www.chictr.org.cn under the registration number ChiCTR2100050543.

Patients will be randomly assigned to one of two groups: an experimental group (EG) and a control group (CG). While all participants will receive routine SLT, the EG will also receive real TMS while the CG will receive sham TMS. The intervention consists of 10 sessions over 2 weeks. The outcomes will be measured at three time points: baseline (T0), 3–5 days before the first session; post-intervention (T1), 3–5 days after the last session; and follow-up (T2), 12 weeks after the last session. The flow chart of this study protocol is shown in Figure 1.

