#### Sample size

To date, none of studies has investigated the effects of cerebellar cTBS on speech impairment in patients with PD. However, our previous study reported positive effects of cerebellar cTBS on impaired auditory-vocal integration in patients with SCA (Lin et al., 2022), who similarly showed abnormally enhanced vocal compensations for pitch perturbations (Li et al., 2019). Based on the obtained partial η^2^ value of 0.559 in that study, we performed an estimation of effect size using G*Power software (version 3.1). Specifically, we used *a priori* F-tests for repeated-measures within-between interaction to determine the required sample size for our study. Our calculations indicated that a total sample size of 16 participants would be necessary to achieve a power of 0.95 and an alpha level of 0.05, considering the presence of two groups. The chosen sample size allows us to adequately investigate the research question while considering resource constraints. To account for potential dropouts and data quality issues, we increased the sample size by 20%, resulting in a final sample size of at least 10 participants per group. However, it is important to note that this sample size calculation is based on the immediate aftereffects of cerebellar cTBS on speech impairments in patients with SCA. Therefore, this study protocol will recruit a total of 40 participants, with 20 participants allocated to each group, for a more conservative approach.

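### The stated analysis set (anyone with at least one post-intervention assessment) does not fit the named three-visit RM-ANOVA, which in its classical form keeps only patients with all three visits

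*Protocol article*

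**What the plan says.** Two sentences of the protocol article's Statistical analysis section matter here.

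- **Analysis set:** "All patients with PD who have at least one post-intervention assessment will be included in the analysis".
- **Model:** "A 2 × 3 two-way repeated-measures analysis of variance (RM-ANOVA) with factors of group (real cTBS, sham cTBS) and time", where the levels of time are "pre-intervention, post-intervention, 12-week follow-up". This one model is assigned to speech functions, neurobehavioural measures of vocal motor control and quality of life, and so to all the primary outcomes. Pairwise post hoc comparisons with Bonferroni adjustment follow from it. The software is SPSS version 20.

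Study design sets the visits: "post-intervention (T1), 3–5 days after the last session; and follow-up (T2), 12 weeks after the last session". The last visit thus comes nearly three months after treatment ends.

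Sample size expects some loss: "To account for potential dropouts and data quality issues, we increased the sample size by 20" per cent. That allowance is applied to a calculated total of 16. The trial then plans for 40, with 20 per group.

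**The concern.** Each sentence is clear alone, but together they cannot both be followed once a patient misses a visit. The analysis set asks for one post-intervention assessment. A classical RM-ANOVA with a three-level time factor needs a value at every level and deletes any patient without one. Deletion is separate for each outcome, so the voice, event-related potential and questionnaire results could each rest on different patients.

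Three things are at stake.

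- **Description:** the report would present a completers analysis as an analysis of everyone with post-intervention data.
- **Precision:** post-intervention values that were observed would be discarded because a later visit was missed, even in the comparison of baseline with post-intervention.
- **Bias:** if staying until 12 weeks depends on how the patient had responded by the post-intervention visit, the completers differ from the randomised groups.

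**Working it through.** **1. The plan's own figure.** Inputs from Sample size: "Based on the obtained partial η^2^ value of 0.559 in that study"; two groups; "a total sample size of 16 participants would be necessary to achieve a power of 0.95 and an alpha level of 0.05".

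- f² = 0.559 / (1 − 0.559) = 1.268, so f = 1.126.
- With k = 2 groups, m = 2 measurements and the convention in which the effect size is taken as SPSS reports it, λ = f²(N − k)(m − 1).
- At N = 16, λ = 1.268 × 14 × 1 = 17.75. On F(1, 14) the power is 0.974.
- At N = 14, λ = 1.268 × 12 = 15.21 and the power is 0.947, just short. So 16 is the smallest even total.
- Allowance: 16 / 0.8 = 20, and 16 × 1.2 = 19.2 also rounds up to 20.

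The sample size reproduces under this convention and is not in dispute.

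**2. Patients in the stated set against patients the model can use.** The total of 40 is from the plan. The article gives no missingness by visit, so all rates below are assumptions.

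| Assumed loss | Meets the stated rule | All three visits |
|---|---|---|
| 10% miss the 12-week visit only | 40 | 40 × 0.90 = 36 |
| 20% miss the 12-week visit only | 40 | 40 × 0.80 = 32 |
| Independent: 5% miss post-intervention, 20% miss 12 weeks | 40 × (1 − 0.05 × 0.20) = 39.6 | 40 × 0.95 × 0.80 = 30.4 |
| Independent: 10% and 20% | 40 × (1 − 0.10 × 0.20) = 39.2 | 40 × 0.90 × 0.80 = 28.8 |
| Dropout: 10% gone by post-intervention, 20% by 12 weeks | 36 | 32 |

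In the second row the interaction error degrees of freedom fall from 2 × (40 − 2) = 76 to 2 × (32 − 2) = 60. A mixed model on the same data keeps all 40 patients and 120 − 8 = 112 of the 120 observations.

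**3. Power at the planning effect.** With m = 3 and the same convention, λ = 1.268 × (N − 2) × 2. At N = 32 this is 1.268 × 30 × 2 = 76.1, and the power is above 0.999. It stays above 0.999 at N = 28.

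**4. Power at a smaller effect.** Assumptions, none from the article: a sustained 0.8 SD difference at both post-intervention visits, equal correlation 0.5 between visits, and random loss split equally between arms.

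- Group differences over time are (0, 0.8, 0.8), with mean 0.533. The sum of squared deviations is 0.284 + 0.071 + 0.071 = 0.427.
- λ = (n per arm / 2) × 0.427 / (1 − 0.5).
- 20 per arm: λ = 10 × 0.427 / 0.5 = 8.53; F(2, 76) gives power 0.73.
- 18 per arm (10% loss): λ = 7.68; F(2, 68) gives 0.68.
- 16 per arm (20% loss): λ = 6.83; F(2, 60) gives 0.62.

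Simulation of the same setting agrees, with about 0.72 to 0.74 falling to 0.61 to 0.63.

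**5. Bias.** Under random loss the completers' estimate is unbiased. If loss before 12 weeks depends on the post-intervention response and does so differently by arm, the completers' post-intervention contrast shifts. The size depends wholly on the assumed mechanism.

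**The case against.** **The listwise step is an inference.** The article names SPSS and RM-ANOVA but no procedure, and the same group-by-time structure fitted with SPSS MIXED would keep incomplete patients. This is fair, but RM-ANOVA ordinarily means the classical form, and nothing in the article points elsewhere.

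**Missing-data rules commonly sit in a SAP.** An imputation rule there could reconcile the two sentences. For that reason the absence of such a rule is not the point. The point is that the article fixes both a set and a method, and the two do not fit.

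**Power is ample.** At the planning effect this is true, and 32 completers is twice the calculated 16. But Sample size itself concedes that the effect comes from immediate aftereffects in another disease, so a smaller effect has to be considered.

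A reader might also infer more than the documents support:

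- *That incomplete patients vanish from every test.* They do not. The functional connectivity comparison in MRI data uses post- minus pre-intervention maps, so a patient missing only the 12-week visit stays in. The baseline comparisons are likewise unaffected.
- *That rejected voice or EEG recordings remove patients.* Those sections reject individual trials and average the rest. No rule discards a whole visit.
- *That the plan forecasts 8 of 40 missing the last visit.* The 20% is a combined allowance for dropout and data quality on a calculated 16. It does not predict 12-week attendance.
- *That the bias has a known size.* One invented scenario has poor responders leaving only the real-stimulation arm. It moves a true 0.80 SD effect to about 0.98 SD at correlation 0.5, or about 0.93 SD at 0.7. Nothing in the article suggests that pattern, so these figures show direction only.

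**Conclusion.** The conflict stands for the outcomes assigned to the RM-ANOVA. Following both sentences would give a completers analysis described as the broader set, and would discard observed post-intervention data. This rests on reading RM-ANOVA in its classical form and on there being some missing visits. With complete data the conflict has no effect.

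The practical size cannot be fixed from the document. Under the assumed 10% to 20% loss of the 12-week visit alone, 4 to 8 of 40 patients would be in the stated set but outside the model. The cost in power is negligible at the planning effect and about 0.11 (0.73 to 0.62) at the smaller assumed effect with 20% random loss. Bias is possible but not quantifiable here. Because the model covers all the primary outcomes, the two sentences should be reconciled before unblinding.

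**What to change.** For the outcomes now assigned to the RM-ANOVA, name a likelihood-based mixed model for repeated measures, fitted with the MIXED procedure in SPSS. Take the post-intervention and 12-week values as outcomes, with arm, visit, arm × visit and baseline as fixed effects. Include every randomised patient with either post-intervention value, and take the post-intervention and 12-week contrasts from this model. Report the completers RM-ANOVA as a sensitivity analysis, with the number of patients contributing to each outcome.

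Restating the set as complete cases, or naming an imputation rule, would also remove the contradiction. The first would still discard observed data, however, and the mixed model serves the stated set directly.

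The cost is a change of wording and slightly more analysis work in the same software. The mixed model relies on data being missing at random given the observed values, and the plan should say so.

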### Randomization, allocation, and blinding

We will use block randomization with a block size of 4 and a 1:1 allocation ratio to assign patients with PD who pass the screening to either the experimental or control group. Randomization will be stratified by gender and age. An independent statistician, who is not be involved in participant enrollment, assessment, or intervention, will generate the randomization sequence. Allocation concealment will be ensured using sealed opaque envelopes, and each envelope will bear a serial number on the outside and a group number on the inside. After baseline assessments, an independent research assistant will open the envelopes in order and assign participants to one of the two groups based on the group number enclosed. Participants, outcome assessors, and data analysts will be blinded to the allocation and intervention.

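### The 2 × 3 RM-ANOVA treats the pre-randomisation value as an outcome and adjusts for nothing; modelling T1 and T2 with baseline, gender and age as covariates would be more efficient and would estimate the effect directly

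*Protocol article*

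**What the plan says.** Under Statistical analysis, the effect of cTBS on speech function, vocal motor control and quality of life is tested by "A 2 × 3 two-way repeated-measures analysis of variance (RM-ANOVA) with factors of group (real cTBS, sham cTBS) and time". The levels are given as "time (pre-intervention, post-intervention, 12-week follow-up) will be used to investigate the effects of cerebellar cTBS on speech functions", so T0 is analysed as an outcome level alongside T1 and T2. No covariate appears. Follow-up comparisons are described only by saying that "pairwise correction will be performed using Bonferroni comparison adjustment"; no between-arm contrast at a named visit is singled out.

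Baseline enters elsewhere in the section only through tests between arms: "Baseline measures will be compared between groups using two-sample" t-tests, and a chi-square test for gender.

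Under Randomization, allocation, and blinding, "Randomization will be stratified by gender and age", and the envelopes are opened after the baseline assessments.

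The analysis set is defined so that "All patients with PD who have at least one post-intervention assessment will be included in the analysis".

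**The concern.** T0 is measured before allocation, so its expected between-arm difference is zero. Used as an outcome level it carries no treatment information; used as a covariate it removes variance from T1 and T2. The planned model has three consequences:

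- The group main effect averages an untreated visit with two treated ones.
- The time effect is shared by both arms, because both receive speech-language therapy.
- The 2-df group-by-time interaction is the only term that bears on cTBS. It does not itself estimate the real-minus-sham difference at either visit.

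The baseline t-tests and chi-square test do not make up for this. After proper randomisation any imbalance is due to chance, and testing for it adjusts nothing. The stratification factors are also absent from the model, so the analysis does not match the randomisation. With 20 patients per arm, precision that the collected data could provide should not be left unused.

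**Working it through.** **The plan's own figure.** Sample size starts from a partial eta squared "value of 0.559 in that study" and uses "F-tests for repeated-measures within-between interaction to determine the required sample size for our study". This gives f = √(0.559/0.441) = 1.126 and f² = 1.268. With the noncentrality defined as f²(N − 2)(m − 1) and m = 2 measurements, N = 16 gives 1.268 × 14 = 17.7 and power 0.974, while N = 14 gives 0.947. The stated total of 16 is therefore reproduced, with two measurements rather than the three in the planned analysis. At this effect size, power with N = 40 is essentially 1 under either analysis, so the plan's own input shows no loss.

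**Like-for-like comparison.** Both tests below have 2 df for the treatment effect and use both post-intervention visits.

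Inputs: n = 20 per arm and two-sided alpha 0.05 (from the document); compound symmetry, rho, and effects d1 at T1 and d2 at T2 in SD units (assumed; the document gives none of them).

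*Planned interaction.* λ = (n/2) × Σ(d_t − d̄)² / (1 − rho) over (0, d1, d2), with 2 and 76 df. For d1 = d2 = 0.8 and rho = 0.5: Σ = 0.64 × 2/3 = 0.427, so λ = 10 × 0.427/0.5 = 8.53 and power is 0.73.

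*Joint baseline-adjusted test of T1 and T2.* Given T0, the residual variance is 1 − rho² and the covariance is rho − rho². Then λ = (n/2) × d′S⁻¹d / (1 + 1/36), with 2 and 36 df; the divisor allows for chance imbalance in the covariate. For d1 = d2 = 0.8 and rho = 0.5: d′S⁻¹d = 2 × 0.64/[(1 − 0.5)(1 + 2 × 0.5)] = 1.28, so λ = 12.8/1.028 = 12.45 and power is 0.87.

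The same formulas give:

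| Effect (T1, T2) | rho | Planned interaction | Joint adjusted test |
|---|---|---|---|
| 0.8, 0.8 | 0.3 | 0.57 | 0.82 |
| 0.8, 0.8 | 0.5 | 0.73 | 0.87 |
| 0.8, 0.8 | 0.7 | 0.92 | 0.955 |
| 0.8, 0.8 | 0.8 | 0.99 | 0.99 |
| 0.8, 0.4 or 0.4, 0.8 | 0.5 | 0.595 | 0.71 |
| 0.8, 0 | 0.5 | 0.73 | 0.75 |
| 0.8, 0 | 0.7 | 0.92 | 0.92 |

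Simulation with 20,000 replicates per setting agreed with these values. Under the null, both tests rejected close to 5% of the time.

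*Group main effect.* With a sustained 0.8 SD effect, averaging in T0 shrinks the expected difference to 0.8 × 2/3 = 0.53 SD. Simulated power at rho 0.5 is 0.53.

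*Gender and age.* The calculation includes neither. An effect of gender or age that is constant over visits cancels within a patient, so omitting them costs the interaction little.

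**The case against.** **Validity.** The planned test holds its type I error with complete data, and nothing in the section makes the choice of model depend on the baseline tests. This stands: the point concerns efficiency and estimation, not invalidity.

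**Intended test.** Sizing on the within-between interaction suggests that efficacy was never meant to rest on the group main effect. That is fair, so the dilution of the main effect is a reason not to use it rather than the centre of the point.

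**Post hoc comparisons.** Bonferroni pairwise comparisons are planned and could locate a difference in time. They do exist, and detail on contrasts and intervals may sit in a fuller document. But comparisons drawn from this model would still lack baseline adjustment, and the model itself is fixed in the article.

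**The document's own effect.** At partial eta squared 0.559 there is no power to gain. However, the Sample size section itself notes that this value reflects immediate aftereffects in another disease and doubles recruitment to be conservative, so it is weak evidence that precision is not needed.

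**Stronger readings that the document does not support.** A reader might infer that a baseline-adjusted contrast at T1 alone would recover power at no price. It changes the question from T1 or T2 to T1 only. It looks better when the effect fades (0.80 against 0.595 at rho 0.5 for 0.8 then 0.4 SD) and much worse when the effect grows (0.29 against 0.595 for 0.4 then 0.8 SD). The document names neither visit as primary and does not say which pattern is expected. A reader might also infer that leaving out gender and age loses power; for the within-subject interaction, no such loss is shown.

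**Conclusion.** The point holds as an avoidable inefficiency and a weakness in estimation. The article fixes a model that treats a pre-randomisation value as an outcome, adjusts for nothing, and ignores the stratification factors.

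The size of the loss depends on rho and on the pattern of effect, and the document gives neither. For a sustained 0.8 SD effect under compound symmetry, baseline adjustment is worth about 25 percentage points of power at rho 0.3, 14 at rho 0.5, 3 to 4 at rho 0.7, and practically nothing at rho 0.8. With 0.8 SD at one visit and 0.4 SD at the other, it is worth about 11 to 12 points at rho 0.5. With a T1-only effect there is little or no gain from rho 0.5 upwards. All figures assume complete data.

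Adding gender and age is justified by agreement with the randomisation, not by a power claim for the interaction.

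**What to change.** Replace the 2 × 3 RM-ANOVA with a model whose outcomes are T1 and T2, with group, time and group-by-time as fixed effects and the baseline value, gender and age as covariates. A mixed model is a natural choice. It also keeps patients who have only one post-intervention assessment, as the stated analysis set requires; a classical RM-ANOVA drops anyone missing a visit. Report the adjusted real-minus-sham difference with a 95% CI at T1 and at T2. If one overall test is wanted, test the two differences jointly. Describe baseline by arm and drop the t-tests and chi-square test.

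Naming T1 as the single primary visit is optional. It would need to be decided in advance, and it would lose power if the effect were larger at 12 weeks.

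The cost is a change of wording in the protocol and a few residual degrees of freedom. All the covariates are already collected, and no extra patients or visits are needed.
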